### 2.4. Participants

The study will enrol 12 adult male or female patients with MNGIE, aged 18 years or above, of any race and who have received no previous treatments. An additional 8 juvenile patients will be enrolled following an Independent Data Monitoring Committee review of an interim analysis of safety data safety and tolerability data. Up to four patients aged 16 years or older may be dosed at the lowest level after 24 patient-months of exposure in patients aged 18 years or over. The starting dose will be Dose Level 1 for both groups, with escalation to the next dose level as described for the adult cohort. Up to four patients aged 12 years or older may be dosed at the lowest dose level (Dose Level 1) after 24 patient-months of exposure in patients aged under 18 years. Juvenile cohorts may escalate to a higher dose or de-escalate to a lower and/or intermediate dose level(s) of EE-TP previously administered. Screening failures and patients withdrawing from the study may be substituted with Independent Data Monitoring Committee recommendations.

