#### 2.4.2. Study Exclusion Criteria

6.Patients who have received a successful liver or bone marrow transplant.7.Patients suitable for allogeneic HSCT.8.Patients with a matched allogeneic HSCT donor.9.Patients with a history of human immunodeficiency virus, hepatitis B infection, or an active hepatitis C infection.10.Patients who are severely disabled or with a life expectancy of less than 12 months at Screening based on the opinion of the investigator.11.Female patients who are:
(i)Pregnant, planning a pregnancy, or are unwilling to use contraception;(ii)Breastfeeding or lactating.12.Patients who have donated blood in the 90 days prior to Screening.13.Patients with a confirmed red blood cell count of <3.0 × 10^9^ per mL.14.Patients who have a significant history of alcoholism or drug/chemical abuse within 1 year prior to Screening based on the opinion of the investigator.15.Patients who have an abnormality in heart rate, blood pressure, or body temperature at Screening that increases the risk of participating in the study based on the opinion of the investigator.16.Patients who have an abnormality in the 12-lead electrocardiogram at Screening that increases the risk of participating in the study based on the opinion of the investigator.17.Patients who have, or have a history of, any clinically significant neurological, gastrointestinal, renal, hepatic, cardiovascular, psychiatric, respiratory, metabolic, endocrine, haematological, or other major disorder (except for disorders associated with MNGIE that do not constitute a risk when taking the study drug and would not interfere with the study objectives) based on the opinion of the investigator.18.Patients with any current malignancy, or a history of malignancy within 5 years prior to Screening, with the exception of adequately treated or excised non-metastatic basal cell or squamous cell cancer of the skin or cervical carcinoma in situ.19.Patients who are currently enrolled in, are planning to participate in, or have discontinued within the last 30 days from a clinical study involving an investigational medicinal product or are concurrently enrolled in medical research judged not to be scientifically or medically compatible with EE-TP.20.Patients with any medical condition which would make the patient unsuitable for enrolment or could interfere with the patient’s participation in, or completion of, the study based on the opinion of the investigator.

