### 2.6. Trial Endpoints

#### 2.6.1. Efficacy Endpoints

The primary efficacy endpoint will be the mean absolute change from baseline in body mass index (BMI) at 24 months. The secondary efficacy endpoints will be the mean absolute change from baseline in BMI at Day 63 and 3, 6, 9, 12, 15, 18, and 21 months, plus the change from baseline at 63 days and 3, 6, 9, 12, 15, 18, 21, and 24 months in: (i) The proportion of patients who require TPN; (ii) Handgrip dynamometry; (iii) RODS; (iv) 10 m walk test; (v) EuroQo-5D; (vi) CGI-I; (vii) PROMIS short form scales; (viii) PGIC; (ix) Neurological examination tests; and (x) VAS for the most disabling symptom.

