### 2.8. Statistical Analyses

Statistical analyses will be primarily descriptive. Analyses will be performed using Statistical Analysis Software^®^ (Version 9.2 or higher, SAS Institute, Cary, NC, USA). For continuous data, summary statistics will include the arithmetic mean, arithmetic standard deviation, median, lower and upper quartiles, plus minimum, maximum, and number. For log normal data, summary statistics, including the geometric mean and geometric coefficient of variation, will also be presented. For categorical data, frequency counts and percentages will be presented. Data listings will be provided for all patients up to the point of withdrawal, with any patients excluded from the relevant population indicated. For the calculation of summary statistics and statistical analysis, unrounded data will be used.

For each study participant the change from baseline will be calculated by subtracting their mean baseline value from the value at the specific time point. The mean change from baseline will be derived as the arithmetic mean of all individual patients’ change from baseline values.

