#### 2.8.5. Interim Analysis

An interim review of data will be conducted after each of the twelve-adult treatment naïve patients has been exposed to EE-TP for at least one year. This interim time point has been chosen to assess and confirm the potential utility of EE-TP in this population, and to provide potential early access of EE-TP in this population. The exposure for a patient at the interim stage could exceed one year if a patient is recruited early on into the study.

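### Substitution is not limited to the time before first dose, and the 24-month BMI mean and interim trigger rest on patients who stay, so the result may lean towards stabilisation

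*Protocol article*

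**What the plan says.** All references are to the protocol article.

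- **Substitution (2.4).** "Screening failures and patients withdrawing from the study may be substituted with Independent Data Monitoring Committee recommendations". One sentence covers screening failures and withdrawals alike, and first dose is not used as a dividing line. Section 2.7 sets twelve treated adults as a minimum.
- **Primary endpoint (2.6.1).** "The primary efficacy endpoint will be the mean absolute change from baseline in body mass index (BMI) at 24 months".
- **Estimator (2.8).** Each patient's change is found by "subtracting their mean baseline value from the value at the specific time point". Then: "The mean change from baseline will be derived as the arithmetic mean of all individual patients’ change from baseline values".
- **Withdrawn patients' data (2.8).** "Data listings will be provided for all patients up to the point of withdrawal, with any patients excluded from the relevant population indicated".
- **Interim (2.8.5).** The review takes place after each of the twelve adults "has been exposed to EE-TP for at least one year". Its stated purposes are to confirm the product's potential usefulness and to open possible early access.
- **Eligibility (2.4.2).** Criterion 10 excludes severe disability and "life expectancy of less than 12 months at Screening". Criterion 20 excludes, in the investigator's opinion, conditions that could stand in the way of completing the study.
- **Yardstick (Discussion).** A BMI that stays within ±0.2 kg/m² is to count as clinically significant.

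**The concern.** Each of the three rules works in favour of patients who remain. A dosed patient who withdraws can be replaced. A patient without a 24-month BMI has no 24-month change to average. The interim condition can be satisfied only by patients who reach one year of exposure.

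Losses are foreseeable. The Discussion describes a steadily worsening, fatal disease with a mean age at death of 37.6 years, and an adult expected to live 12 to 24 months is not excluded by the life-expectancy criterion. If the adults who are lost are mainly those losing weight, their decline drops out of the primary mean. There is no control arm in which the same attrition would show. The Discussion also argues that any halt or improvement would have no credible explanation other than treatment, and selective loss would be one. At stake are the stabilisation claim at 24 months and the interim view on usefulness and early access.

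**Working it through.** **1. No figure to reproduce for N.** Section 2.7 states that the sample size does not come from a calculation, and no dropout rate is given. The BMI scale can be checked from the mean heights in the Discussion: 0.2 × 1.70² = 0.58 kg (men) and 0.2 × 1.591² = 0.51 kg (women). This agrees with the stated figure of about 0.5 kg, so the stabilisation margin is narrow.

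**2. Size of the shift.** Let k adults be lost and let the gap be the mean change in completers minus the mean change in those lost.

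- No substitution: shift = (k/12) × gap
- Each lost adult replaced by one who completes: shift = (k/(12 + k)) × gap
- Gap that moves the mean by 0.2 kg/m² without substitution: 0.2 × 12/k

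**3. Illustration (assumed).** Three of 12 adults lose 1.0 kg/m² and leave; nine are unchanged. For those lost, the change at leaving stands in for a 24-month value.

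- All dosed, no substitution: (3 × -1.0 + 9 × 0)/12 = -0.25; completers 0.00
- Three stable substitutes, 15 dosed: (3 × -1.0 + 12 × 0)/15 = -0.20; completers 0.00

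**4. Other numbers lost, with an assumed gap of 1.0 kg/m².**

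| k lost | Shift, no substitution | Shift, with substitutes | Gap giving a 0.2 shift, no substitution |
|---|---|---|---|
| 1 | 0.08 | 0.08 | 2.4 |
| 2 | 0.17 | 0.14 | 1.2 |
| 3 | 0.25 | 0.20 | 0.8 |
| 4 | 0.33 | 0.25 | 0.6 |

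For k = 3, the gap of 0.8 kg/m² is 0.8 × 1.591² = 2.0 kg for women and 0.8 × 1.70² = 2.3 kg for men. Substitution does not create the shift and slightly dilutes it. What it does is bring the number with a 24-month value back to 12, so the loss is less visible.

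**5. Dependence on why patients leave.** Simulation, 400,000 draws per setting, assumed true mean change -0.5 kg/m², logistic loss depending on the 24-month change (log-odds 1 per SD where related).

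| SD | Lost | Who is more likely to leave | Completer mean | Bias |
|---|---|---|---|---|
| 1.0 | 15% | decliners | -0.37 | +0.13 |
| 1.0 | 25% | decliners | -0.29 | +0.21 |
| 1.0 | 40% | decliners | -0.17 | +0.33 |
| 0.7 | 25% | decliners | -0.35 | +0.15 |
| 1.0 | 25% | unrelated to BMI change | -0.50 | 0 |
| 1.0 | 25% | improvers | -0.71 | -0.21 |

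In the 40% row the completer mean falls inside ±0.2 although the true mean does not.

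**6. Interim trigger.** Suppose one of the first twelve adults dies or stops at month 6. The condition in 2.8.5 can then never be met for those twelve; taken literally, only a replacement who reaches one year can satisfy it.

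**The case against.** The strongest reply is that the article never declares a completer analysis. Section 2.8 defines a change score and its average and refers to populations that it does not set out. Rules for missing data and deaths commonly sit in the statistical analysis plan, so their absence here is no defect. This stands: a reader might infer that the primary population is completers, but that is only what the formula yields when applied as written.

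A reader might also infer that a substitute displaces the withdrawn patient from the analysis. The text does not say so. Substitution is optional, needs a committee recommendation, and fits with twelve being a minimum. Some withdrawals will fall in the 90-day run-in, before any dose. All this stands, but the sentence still leaves post-dose replacement open and does not say what then happens to the dosed patient's data.

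Eligibility is tighter than the life-expectancy limit alone suggests, because criteria 10 and 20 also exclude severe disability and conditions that could prevent completion. That lowers the expected loss without removing it.

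The direction of bias is not fixed. The Discussion foresees the product as a bridge until a transplant donor is found, so a patient might leave without having failed.

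Attrition would not be wholly concealed: summaries give the number of patients, BMI change is reported at eight earlier time points, and the monitoring committee sees withdrawals. These show that patients are missing, but they do not put the missing declines back into the 24-month mean.

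Finally, a patient who has died has no 24-month BMI, so an all-dosed mean needs a convention. This is a reason to report a proportion beside the mean.

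**Conclusion.** The concern holds in a conditional form. Applied as written, the substitution rule, the 24-month mean and the interim trigger favour patients who remain, and in twelve uncontrolled adults this may turn a decline into apparent stabilisation. In the assumed case of three losses the shift is 0.25 kg/m² without substitution and 0.20 with it, against a margin of 0.2. With one or two losses and a gap of 1.0 kg/m² it is 0.08 to 0.17.

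These sizes rest on an assumed number lost and an assumed gap; the article gives neither. Bias towards stabilisation is the likelier direction in a fatal wasting disease, but it is zero if loss is unrelated to BMI change and reversed if improvers leave. The documents therefore do not support saying that the primary result is biased, or that treatment failures will be removed from it. They do support correcting the three rules before data accrue.

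**What to change.** 1. **Section 2.4.** Limit substitution to patients who have not yet been dosed. After the first dose, any new patient is an addition, and the withdrawn patient stays in all efficacy and safety analyses. This fits the minimum of twelve in 2.7.
2. **Section 2.8.3.** Beside the mean, report the proportion of all dosed adults who are alive, in follow-up and have a 24-month BMI change of at least -0.2 kg/m², counting death or withdrawal as failure. Add a sensitivity analysis of the mean using all scheduled on-treatment BMI values. A mixed model is one option, not a requirement. Table 4 already places BMI at the recurring 2- to 4-weekly visits. An adult lost before those visits adds little to that analysis, which is a further reason for the proportion.
3. **Section 2.8.5.** Trigger the interim when each of the first twelve dosed adults has completed 12 months or has died or discontinued, and include all twelve.

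The cost is wording in the protocol and analysis plan, with no new data. The downside is that the reported effect may look less favourable, and more than twelve adults may be dosed if additions are made. Section 2.13 describes the trial as not yet recruiting. The change is best made before enrolment, because in an open-label trial a later choice could follow the results.

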#### 2.4.1. Study Inclusion Criteria

Patients must be aged 18 years or older. The age range will be extended to include:
(i)Patients aged 16 years or older after 24 patient-months of exposure in those aged 18 years or over;(ii)Patients aged 12 years or older after 24 patient-months of exposure in patients aged under 18 years of age at the time of enrolment.Patients must be diagnosed with MNGIE by demonstrating all of the following:
(i)<18% normal thymidine phosphorylase activity in the buffy coat;(ii)>3 μmol/L plasma thymidine;(iii)>5 μmol/L plasma deoxyuridine;(iv)Confirmation of the presence of biallelic pathogenic variants in TYMP by sequencing.Patients must be able to undergo study procedures.Patients must agree to either remain completely true abstinent or to use 2 effective contraceptive methods from Screening until completion of the Follow-up Visit.Patients must be willing to sign and date the written Informed Consent Form.

#### 2.4.2. Study Exclusion Criteria

6.Patients who have received a successful liver or bone marrow transplant.7.Patients suitable for allogeneic HSCT.8.Patients with a matched allogeneic HSCT donor.9.Patients with a history of human immunodeficiency virus, hepatitis B infection, or an active hepatitis C infection.10.Patients who are severely disabled or with a life expectancy of less than 12 months at Screening based on the opinion of the investigator.11.Female patients who are:
(i)Pregnant, planning a pregnancy, or are unwilling to use contraception;(ii)Breastfeeding or lactating.12.Patients who have donated blood in the 90 days prior to Screening.13.Patients with a confirmed red blood cell count of <3.0 × 10^9^ per mL.14.Patients who have a significant history of alcoholism or drug/chemical abuse within 1 year prior to Screening based on the opinion of the investigator.15.Patients who have an abnormality in heart rate, blood pressure, or body temperature at Screening that increases the risk of participating in the study based on the opinion of the investigator.16.Patients who have an abnormality in the 12-lead electrocardiogram at Screening that increases the risk of participating in the study based on the opinion of the investigator.17.Patients who have, or have a history of, any clinically significant neurological, gastrointestinal, renal, hepatic, cardiovascular, psychiatric, respiratory, metabolic, endocrine, haematological, or other major disorder (except for disorders associated with MNGIE that do not constitute a risk when taking the study drug and would not interfere with the study objectives) based on the opinion of the investigator.18.Patients with any current malignancy, or a history of malignancy within 5 years prior to Screening, with the exception of adequately treated or excised non-metastatic basal cell or squamous cell cancer of the skin or cervical carcinoma in situ.19.Patients who are currently enrolled in, are planning to participate in, or have discontinued within the last 30 days from a clinical study involving an investigational medicinal product or are concurrently enrolled in medical research judged not to be scientifically or medically compatible with EE-TP.20.Patients with any medical condition which would make the patient unsuitable for enrolment or could interfere with the patient’s participation in, or completion of, the study based on the opinion of the investigator.

### 2.5. Interventions

#### 2.5.1. Preparation and Administration of Erythrocyte Encapsulated Thymidine Phosphorylase (EE-TP)

On the morning of each treatment cycle patients will undergo venesection for the collection of 120–360 mL of blood for the manufacture of EE-TP. The volume of blood collected will be dependent on the patient’s haematocrit, red cell count, and the dose of EE-TP to be administered. EE-TP will be administered as an intravenous infusion, within 30 min of the completion of manufacture, according to the specified study protocol, using a standard intravenous infusion set with a micro-aggregate filter in-line. 

#### 2.5.2. Assessments

The following information will be recorded for all potential patients as part of the screening assessments: Informed consent, inclusion/exclusion criteria, demography, including sex, race and age, medical history, and concomitant medication use (Table 3).

Each patient will be required to undergo the following assessments during the screening and run-in phases (Table 3) and treatment and follow-up phases (Table 4) at the study times indicated: Vital signs measurement, 12-lead electrocardiogram (ECG), body weight (kg) and height (m), physical examination, pregnancy test (female patients only), adverse event recording, total parenteral nutrition (TPN) use, handgrip strength using handgrip dynamometry, disability measured using the Rasch built Overall Disability Scale (RODS), ambulatory function measured using the 10 m walk test, gastrointestinal symptoms (abdominal pain, diarrhoea, disrupted swallowing, gas and bloating, gastroesophageal reflux, and nausea and vomiting) measured using the Patient-Reported Outcomes Measurement Information System (PROMIS) short form scales, distal sensory impairment and areflexia or motor strength using neurological examinations, MRI brain, abdominal ultrasound, nerve conduction studies and electromyography, neuro-ophthalmology and quality of life measured using EuroQol 5 Dimension (EuroQol-5D), Clinical Global Impression-Improvement Scale (CGI-I), Patient Global Impression of Change (PGIC), and visual analogue scale (VAS) for determining the severity of the patient’s most disabling symptom.

#### 2.5.3. Clinical Laboratory and Pharmacodynamic Evaluations

Blood and urine samples will be collected for haematology, serum biochemistry and urinalysis evaluations and for the longitudinal monitoring of thymidine and deoxyuridine concentrations at the times indicated in Table 3 and Table 4. Blood samples will also be collected for the measurement of anti-thymidine phosphorylase antibodies and neutralizing antibodies, and for the exploratory analysis of fibroblast growth factor 21 (FGF21), growth differentiation factor 15 (GDF15), mtDNA, messenger RNA (mRNA), microRNA (miRNA), and lipidomics, proteomics, and other markers of mitochondrial condition (Table 3 and Table 4).

### 2.6. Trial Endpoints

#### 2.6.1. Efficacy Endpoints

The primary efficacy endpoint will be the mean absolute change from baseline in body mass index (BMI) at 24 months. The secondary efficacy endpoints will be the mean absolute change from baseline in BMI at Day 63 and 3, 6, 9, 12, 15, 18, and 21 months, plus the change from baseline at 63 days and 3, 6, 9, 12, 15, 18, 21, and 24 months in: (i) The proportion of patients who require TPN; (ii) Handgrip dynamometry; (iii) RODS; (iv) 10 m walk test; (v) EuroQo-5D; (vi) CGI-I; (vii) PROMIS short form scales; (viii) PGIC; (ix) Neurological examination tests; and (x) VAS for the most disabling symptom.

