### 2.3. Trial Design

The trial is a Phase 2, multi-centre, multiple dose, open label trial without a control which will be conducted in a maximum of five sites in Europe and Israel, with all patients receiving EE-TP. For each patient, the overall study duration will be 31 months, consisting of a 28 day screening phase, a 90 day run-in phase, a 24 month open-label treatment phase, and a 90 day follow-up phase. A schematic of the proposed study design is presented in Figure 2.

Patients will be screened for eligibility from Day −120 to Day −92. If eligible, patients will then enter the run-in period, from Day −91 to pre-dose on Day 0, in which key aspects of their overall clinical condition and metabolite levels will be recorded. The variability in these clinical and metabolic parameters is currently unknown, and these data will primarily serve to act as each patient’s own pre-treatment/control observations.

Prior to entering the treatment phase, patients will attend the study site for pre-treatment assessments and to determine continued study eligibility either the day before dosing (Day –1) or in the morning of the day of dosing (Day 0). For the first four treatment cycles, the administration will be every 21 days, with the administration of EE-TP at the same time of day (±2 h). The first dose (Treatment Cycle 1) of EE-TP will be administered on day 0, with subsequent doses on Days 21, 42, and 63 (Treatment Cycles 2, 3 and 4, respectively). For Treatment Cycles 1, 2, 3, and 4, patients will leave the study site following dosing and return the next day (Days 1, 22, 43, and Day 64, respectively) for 24 h post-dose assessments. The planned dose levels are presented in Table 2. All patients will receive infusions at Dose Level 1 (~58–65 × 10^10^ erythrocytes encapsulating ~30–49 U TP/10^10^ erythrocytes) for the first 2 treatment cycles (Treatment Cycles 1 and 2). If metabolic correction (defined as plasma thymidine <3 µmol/L and deoxyuridine <5 µmol/L, i.e., below the diagnostic levels for MNGIE) is not achieved, the subsequent 2 treatment cycles (Treatment Cycles 3 and 4) will be administered at Dose Level 2 (~58–65 × 10^10^ erythrocytes encapsulating ~50–69 U TP/10^10^ erythrocytes).

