### 2.7. Sample Size

The sample size for this study is dictated by the rarity of the condition and not by any quantitative statistical considerations or formal sample size calculations. At least 12 adult treatment naïve patients will be treated in this study, with the option to enrol an additional 8 juvenile patients, beyond this original set of 12 patients.

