#### 2.8.3. Efficacy Data Analysis

The changes from baseline for all efficacy endpoints and outcomes will be calculated using data from the run-in period (Day −91 to Day 0) as the baseline. Absolute and percentage changes from baseline in BMI will be plotted. In addition, absolute and percentage changes from baseline in BMI will be recorded against plasma and urine concentrations of thymidine and deoxyuridine. The percentage of patients achieving at least the minimum threshold of weight gain will be presented by dose. Since juvenile patients in the juvenile cohorts will be developing (i.e., growing and maturing) during the study, changes in weight and other efficacy endpoints cannot be reliably attributed to EE-TP, and therefore their data will not be included in the main efficacy analyses, and will be analysed separately.

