## 3. Discussion

Mitochondrial neurogastrointestinal encephalomyopathy is a relentlessly progressive disorder with an invariably fatal outcome, and therefore an early diagnosis and subsequent normalisation of deoxynucleosides is critical to avoid ongoing mitochondrial damage and disease progression. The compassionate treatment of patients with regular infusions of EE-TP demonstrated a reduction or elimination of plasma deoxynucleosides and clinical improvements in patients who received long-term treatment, suggesting that EE-TP is able to reverse some aspects of the disease pathology [18,19]. This study aims to determine the safety, tolerability, pharmacodynamics, and efficacy of multiple doses of EE-TP in patients with MNGIE. In practice, treatment with EE-TP is likely to be sought for patients in whom the risk of mortality from allogeneic HSCT would be too high, and also for those for whom there is no matched donor. Treatment with EE-TP may also be indicated as a rescue or maintenance therapy prior to the availability of a suitable HSCT donor, and for patients who are oligosymptomatic and reluctant to undergo HSCT.

The total sample size of 12 adult treatment naïve patients is not based on a formal statistical calculation; it is a relatively small sample size, but this is expected to be offset by the nature of the condition. MNGIE has a predictable clinical course; it is relentlessly progressive, with a very poor prognosis for life, and it has been reported that the mean age of death is 37.6 years (range 15–54 years) [21]. Therefore, any arrest or improvement of patients’ clinical deficits and/or reduction in mortality should be conspicuous and would not be plausibly explained by factors other than treatment with EE-TP. Clearly, such findings would be highly clinically relevant.

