There are generally no accepted endpoints for clinical studies in patients with MNGIE. This ultra-rare disease usually presents with a combination of cachexia, gastrointestinal dysfunction, and neuromuscular dysfunction. Although weight loss is one of the key features of MNGIE and has a major impact on functional status, individual weight loss trajectories are not typically available in published case series. Weight loss is clearly associated with increased morbidity and mortality, and a decreased quality of life in other chronic diseases for which weight loss is a primary manifestation, including cancer [24], chronic obstructive pulmonary disease [25], chronic heart disease [26], chronic kidney disease [27], and acquired immunodeficiency syndrome [28]. Overall, current evidence shows that weight loss is a valid prognostic marker and is associated with decreased quality of life across different conditions. Additionally, at least in patients with cancer, weight loss and symptoms associated with anorexia cachexia have been shown to have a psychosocial effect, not only on patients, but also on the caregivers and families of those affected [29].

Weight is an objective measurement, which is readily obtained without causing additional burden to patients. Objectiveness is a critical requirement within the context of the planned open label design of this study. Serial measurements of body weight offer the simplest screen for nutritional adequacy and change in nutritional status. The weight and height of a patient are used to formulate the BMI (i.e., calculated by an individual’s body mass divided by the square of his/her height (kg/m^2^)). Since weight loss is essentially a universal feature of MNGIE, any weight gain is highly likely to represent a very sensitive clinical objective. Consequently, the primary clinical endpoint in this study will be mean absolute change from baseline in BMI.

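### The BMI endpoint and the weight-gain count ignore TPN use, so starting or stopping TPN can be scored as gain or loss under EE-TP

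*Protocol article*

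**What the plan says.** The primary endpoint in section 2.6.1 is "The primary efficacy endpoint will be the mean absolute change from baseline in body mass index (BMI) at 24 months", with no condition on nutritional support. Section 2.8.3 calculates changes "using data from the run-in period (Day −91 to Day 0) as the baseline", sets BMI change against plasma and urine thymidine and deoxyuridine, and gives by dose the percentage of patients reaching the weight-gain threshold. TPN appears in none of these analyses. It is a separate secondary endpoint in 2.6.1: "The proportion of patients who require TPN".

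TPN use is recorded three times in run-in (Table 3) and then at Day 63, through treatment and at follow-up (Table 4). No criterion in 2.4.1 or 2.4.2 excludes TPN or requires it to be stable. Section 2.3 describes an "open label trial without a control which will be conducted in a maximum of five sites in Europe and Israel", and section 2.7 says "At least 12 adult treatment naïve patients will be treated in this study".

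The Discussion sets +0.2 kg/m² as the threshold for counting a patient as having gained weight, and regards stabilisation within ±0.2 kg/m² as clinically significant. It also argues: "Since weight loss is essentially a universal feature of MNGIE, any weight gain is highly likely to represent a very sensitive clinical objective". Of any arrest or improvement in clinical deficits, or reduction in mortality, it says that this "would not be plausibly explained by factors other than treatment with EE-TP".

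**The concern.** TPN supplies calories without passing through the gut. The mechanism that the Discussion proposes for EE-TP runs through better intestinal motility and absorption, so weight gained on TPN is not evidence for it. Need for TPN may also move opposite to the patient's condition. A patient whose gut function worsens and who starts TPN may gain weight and be scored a success. One who recovers and stops TPN may lose weight and be scored a failure. The error can therefore go either way.

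Section 2.8.3 already accepts the principle for juveniles: they are kept out of the main efficacy analysis because growth prevents their weight change from being attributed to EE-TP. The same reasoning is not applied to TPN in adults. What is at stake is whether the primary efficacy result can be read as an effect of EE-TP in patients whose TPN changed.

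**Working it through.** **Inputs from the article.** 12 adults (2.7). Threshold 0.2 kg/m², stated to be about 0.5 kg; average heights 170 cm (males) and 159.1 cm (females); average weights 40.3 and 35.5 kg (all Discussion).

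**Inputs not in the article.** Weight gained on TPN, number of patients starting or stopping it, and BMI change in the other patients. These are varied below as assumptions.

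**1. The plan's own figure.** Weight = BMI change × height².
- Males: 0.2 × 1.70² = 0.2 × 2.89 = 0.58 kg.
- Females: 0.2 × 1.591² = 0.2 × 2.531 = 0.51 kg.

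This agrees with the stated 0.5 kg. The quoted BMI of about 14 also checks: 40.3 / 2.89 = 13.9 and 35.5 / 2.531 = 14.0.

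**2. Patient-level count.** A gain of about 0.5–0.6 kg from any source makes a patient a gainer. Each such patient adds 1/12 = 8.3 percentage points overall, and more within a dose level, because 2.8.3 reports the percentage by dose. A loss of the same size after stopping TPN takes a patient out of the ±0.2 band.

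**3. Mean of 12 adults.** Let two patients gain through TPN and let the other ten each change by d. For a mean of m, each TPN patient needs a BMI change of (12m − 10d) / 2. This is converted to kg at the mean height of 1.6455 m (height² = 2.708 m²), with the range for female to male heights in brackets.

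| Change in other ten (assumed) | Mean −0.2 | Mean 0 | Mean +0.2 |
|---|---|---|---|
| d = 0 | no gain needed | no gain needed | 1.2 → 3.2 kg (3.0–3.5) |
| d = −0.5 | 1.3 → 3.5 kg (3.3–3.8) | 2.5 → 6.8 kg (6.3–7.2) | 3.7 → 10.0 kg (9.4–10.7) |
| d = −1.0 | 3.8 → 10.3 kg (9.6–11.0) | 5.0 → 13.5 kg (12.7–14.4) | 6.2 → 16.8 kg (15.7–17.9) |

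Example: for d = −0.5 and m = −0.2, (−2.4 + 5.0) / 2 = 1.3 kg/m², and 1.3 × 2.708 = 3.5 kg.

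The individual count is thus very sensitive to TPN. The mean is sensitive if the other patients are stable. If they decline moderately, two gains of about 3.5 kg still bring it to the edge of the stabilisation band. The larger entries, from about 10 kg, are a quarter or more of the quoted body weights.

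**The case against.** A reader might infer that TPN alone could produce the claimed benefit. The documents do not support that. The benefit claimed is stabilisation, and when ten of twelve patients are held at no change they are already stable without TPN. If they decline, the gains needed for a positive mean are large. The +0.2 kg/m² threshold is also defined for counting patients; the article does not make it a success criterion for the mean, and it is used for the mean here only as a yardstick.

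Other points have weight:
- The article does not say who decides on TPN, how often it starts, or what weight follows.
- Need for TPN is reported at the same nominal times as BMI, use is recorded in run-in, and section 2.8 promises data listings for all patients, so new use can be identified. A net rise in users would be visible.
- The analysis is mainly descriptive, and an analysis plan that is not shown may add TPN analyses.
- The attribution sentence in the Discussion concerns clinical deficits and mortality and does not name BMI.

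These points limit the size of the concern but do not remove it. A proportion of users does not tie TPN to an individual's BMI, does not show increased TPN in an existing user, and hides starts that are offset by stops. The endpoint and count as fixed in the article credit weight gain regardless of TPN, and the Discussion treats any weight gain as a sign of benefit. That is a stated rule, not a detail left open.

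**Conclusion.** The concern holds in this form: the primary BMI change and the weight-gain count use BMI as observed, whatever the TPN use, with no control to separate TPN from EE-TP. Misclassification of individual patients is the firmest part, since about 0.5–0.6 kg is enough. The effect on the mean is conditional. Two TPN patients shift it by 0.2 kg/m² with about 3.0–3.5 kg each if the other ten are unchanged. If the other ten lose 0.5 kg/m², the two need about 3.5 kg each for a mean of −0.2 and about 10.0 kg each for +0.2. All of these gains and declines are assumptions. The direction of any net bias cannot be known in advance.

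**What to change.** In sections 2.6.1 and 2.8.3:

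- **Patient-level count.** Do not count as gained or stabilised a patient with new TPN use after Day 0 relative to run-in, or with increased use if the amount is recorded.
- **Mean BMI change.** Keep the as-observed mean, and report beside it BMI change by TPN status: never, at run-in, started, stopped. The last group shows losses that may follow improvement. Do not simply discard values after TPN starts: that removes deteriorating patients and can flatter the mean.
- **Discussion.** Qualify the statement that improvement would have no plausible explanation other than EE-TP, naming change in TPN as one.

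The cost is small. TPN use is already scheduled in Tables 3 and 4, and section 2.13 says that recruitment has not opened, so the rule can be set before any data are seen. The responder count may become less favourable. Handling increases would require the amount of TPN to be recorded, whereas the tables list only its use.
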